
#### Biochemical profile

Morning fasting blood samples will be obtained from each participant by experienced nursing staff at the Santiago Apóstol Hospital (Miranda de Ebro, Burgos). This procedure will permit measurements of general metabolism (renal function: urea [mg/dL], creatinine [mg/dL], glomerular filtration rate [mL/ min/body surface area]; carbohydrates metabolism: basal glucose [mg/dL], HbA1c [%], fasting insulinemia [μUI/mL], homeostatic model assessment to quantify insulin resistance, HOmeostatic Model Assessment-Insulin Resistance [insulin (μU/L) × glucose (mmol/L)/22.5]; hepatic function: aspartate transaminase [U/L], alanine transaminase [U/L], alkaline phosphatase [U/L]; blood cells: hemoglobin [g/dL], hematocrit [%], leukocytes [/uL], lymphocytes [/uL], neutrophils [/uL], and platelets [/uL]), lipid metabolism (total cholesterol [mg/dL], low-density lipoprotein cholesterol [mg/dL], high-density lipoprotein cholesterol [mg/dL], triglycerides [mg/dL]; oxidative stress: ox-LDL [U/dL]), muscular and myocardial stress (troponin T [μg/L]; total creatine kinase [U/L]; pro-b-type natriuretic peptide [pg/mL]), systemic inflammation (highly sensitive C-reactive protein [mg/L], interleukin-6 [pg/mL], tumor necrosis factor-alpha [pg/mL]) and procoagulant state (D-dimer [ng/mL], fibrinogen [mg/dL]).

#### Mediterranean diet pattern

The dietary habits of participants will be assessed using a validated 137-item food frequency questionnaire (FFQ) including eight items related to seafood [38] and a 24-h recall questionnaire. A trained nurse in face-to-face interviews and group counseling will complete the FFQ. Nutrient intakes will be computed using Spanish food composition Tables [39]. The Mediet adherence is evaluated through a 14-item Mediterranean Diet Adherence Screener (MEDAS), which consists of 12 questions on food consumption frequency and two questions on food intake habits considered characteristics of the Spanish Mediterranean diet [40]. Participants will receive the main dietary recommendations included in the PREDIMED trial [21, 41]. The major characteristics of this diet are: (1) a high consumption of cereals, legumes, nuts, vegetables, and fruits; (2) a relatively high-fat consumption, mostly provided by olive oil; (3) moderate to high fish consumption; (4) poultry and dairy products consumed in moderate to small amounts; (5) low consumption of red meats and meat products; and (6) moderate alcohol intake, usually in the form of red wine [42, 43]. Participants will be encouraged, weighed, and receive advice and nutritional counseling every two weeks to help in their compliance with the dietary recommendations and requirements.

### Intervention/attention control

The AC group will receive Mediet and regular physical exercise recommendations to keep ethical procedures regarding health. In this sense, participants will be advised to participate, without supervision, in at least 30 min of moderate-intensity dynamic aerobic exercise (walking, jogging, cycling, or swimming) 5–7 days per week [13, 44]. Participants will receive information related to HR values regarding moderate exercise intensity domains for the self-monitoring of exercise intensity and will be encouraged to keep a daily record of the performed physical activity.

Exercise groups will receive Mediet recommendations and supervised exercise:HV-HIIT group: high-intensity (HR values up to VT2 to peak intensity or ≥ 85% to < 95% of HR reserve) interval training and HV increasing gradually from 20 min to 40 min and alternating high and moderate intensities at different protocols; andLV-HIIT group: HIIT and low-volume (20 min) alternating high and moderate intensities at different protocols.

### Exercise intervention program

The participants in the HIIT groups will exercise two non-consecutive days per week for 16 weeks under supervision by an exercise specialist and we will also request to continue with their normal activity patterns outside of the study protocol. All the exercises sessions will start and finish with BP monitoring; training intensity will be controlled by HR monitoring (Polar Electro, Kempele, Finland) and through the rate of perceived exertion using the Borg’s original scale (6–20 points). Each session will include a 10-min warm-up with joint mobility (i.e. starting at the top of the body and working the way down, from the neck, shoulders, upper back, hips, and ankles) with continuous leg movement to facilitate the venous return and coordination exercises (e.g. toe-tapping arm circles, heel walks, high knee walk, backwards high knee skip) and a 10-min cool-down period with passive stretching exercises on the floor to ensure a progressive return to the resting values of both HR and BP. The main portion of the training session will consist of aerobic exercises (i.e. one day of the week on the treadmill and the second one on the bike) developing progressively both the volume (i.e. 20 min to 40 min in HV-HIIT, whereas in LV-HIIT the duration will always be 20 min) and intensity. The rationale of mixing bike and treadmill will be to avoid the osteoarticular impact of two treadmill days taking into account the HIIT program. Intensity will be individually tailored to HR at moderate or vigorous intensities, adjusting the speed and incline of the treadmill or the power and speed on the bike to achieve the planned target HR (Table 2). The importance of targeting moderate and high intensity will be emphasized.

**Table 2 Tab2:** Intervention program for high-volume high-intensity (HV-HIIT) and low-volume high-intensity (LV-HIIT) groups on the treadmill and the bike. Volume and intensity progression

	High-intensity interval		Moderate-intensity interval		High-intensity interval		Moderate-intensity interval	
	HV-HIIT treadmill				LV-HIIT treadmill			
Weeks	Volume (min)	Intensity (%HRres)	Volume (min)	Intensity (%HRres)	Volume (min)	Intensity (%HRres)	Volume (min)	Intensity (%HRres)
1–2	8	85	12	65	8	85	12	65
3–4	12	85	13	65	8	85	12	65
5–6	16	90	14	70	8	90	12	70
7–8	16	90	19	70	8	90	12	70
9–10	16	95	24	75	8	95	12	75
11–12	16	95	24	75	8	95	12	75
13–16	16	95	24	75	8	95	12	75
	HV-HIIT bike				LV-HIIT bike			
Weeks	Volume (min)	Intensity (%HRres)	Volume (min)	Intensity (%HRres)	Volume (min)	Intensity (%HRres)	Volume (min)	Intensity (%HRres)
1–2	2–2:30	85	17:30	65	2–2:30	85	17:30	65
3–4	3–3:30	85	21:30	65	3–3:30	85	16:30	65
5–6	4–4:30	90	25:30	70	4	90	16	70
7–8	5–5:30	90	29:30	70	4	90	16	70
9–10	6–6:30	95	33:30	75	4	95	16	75
11–12	7–7:30	95	32:30	75	4	95	16	75
13–16	8	95	32	75	4	95	16	75

Several strategies will be implemented to maximize adherence, including music in all sessions, individualized attention at the intervention sessions, and telephone calls following missed sessions.

#### High-intensity interval training protocol on the treadmill

The high intensity aerobic exercise groups will carry out a 5- to 10-min warm-up period at a moderate-intensity (i.e. HR values between VT1 and VT2 or 65–75% of HR reserve) on the treadmill, before walking two intervals of 4 min at high intensity (i.e. HR values up to VT2 to peak intensity or ≥ 85% to < 95% of HR reserve). The participants will exercise at the lower-intensity limit for the first two weeks of the training period before increasing the intensity towards the upper limit. Between the high-intensity intervals, 3 min of walking at moderate intensity will be conducted. The training session will end with a 4-min cool-down period at moderate intensity. This is a traditional protocol in cardiac rehabilitation programs and research with cardiac patients [15, 45]. This will give a total exercise time of 20 min. While this protocol will be kept in the LV-HIIT group, every two weeks the HV-HIIT will progress to four intervals of 4 min at high intensity and 40 min of total volume (Table 2).

#### High-intensity interval training protocol on the bike

The high-intensity aerobic exercise groups will carry out a 5- to 10-min warm-up period on the bike. After that, the participant will cycle for 30 s at high intensity (i.e. HR values up to VT2 to peak intensity or ≥ 85% to < 95% of HR reserve) followed by 60 s at moderate intensity (i.e. HR values between VT1 and VT2 or 65–75% of HR reserve) [46]. Four repetitions (1 rep = 30 s high intensity followed by 60 s moderate intensity) will be initially performed in both groups and gradually increased to 16 repetitions in the HV group, while eight repetitions will be completed (Table 2) in the LV group. The training session will end with a 4- to 7-min cool-down period at moderate intensity. The protocol design for biking has already been established in cardiac rehabilitation programs [14].

### Participant withdrawal

A participant could leave the study at any time. When withdrawing from the study, the participant should let the research team know that he/she wishes to withdraw. The following are the trial-related reasons for the participant to be discontinued from the trial by the principal investigator: (1) failure to maintain 80% compliance to exercise training sessions or even the last four weeks (minimum eight sessions), to avoid detraining; (2) more than two consecutive weeks without training, to avoid detraining; (3) participant’s condition or disease progresses; (4) participant experiences a serious adverse event (e.g. angina, dyspnea, light-headedness) [47] that requires discontinuation or withdrawal from the study according to the study protocol; or (5) pregnancy.

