### Measurements

The measurements used in the protocol will be taken before and after the intervention period (16 weeks). The study protocol flow of participants is outlined in Fig. 1. The post-intervention test will be scheduled the following week after finishing the 16-week intervention period. The primary outcome variable is cardiorespiratory fitness, measured through VO_2peak_. The secondary outcome variables include left ventricular function, body composition, biochemical profile, vascular endothelial function, dietary adherence, the state of depression and anxiety, and health-related quality of life. The SPIRIT figure showing the respective time points for assessments and intervention is provided in Fig. 2.

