### Data analysis

The primary outcome variable of this study is VO_2peak_. A priori power analysis (G*Power 3 statistical software) [48] was performed to calculate the average sample size. Due to the lack of any source on the effect of VO_2peak_ in MI patients, we speculate a similar increase based on a study of coronary artery disease [49]. Therefore, we assume a mean change of 5.0 mL kg^−1^ min^−1^ and a common standard deviation (SD) of 4.0 for participants allocated to the HIIT groups and a mean change of 3.0 ± 4.0 mL kg^−1^ min^−1^ for participants allocated to the AC group. Based on 1:1:1 randomization to three treatment arms with equal group size, we expect that pre-post intervention differences in our design would be achieved with 177 people (59 each group, α = 0.05, Cohen medium effect size f = 0.23, 80% power). Assuming a maximum loss of follow-up of 10%, the plan will be to recruit a total of 194 individuals. The statistical analysis will be performed using IBM SPSS Statistics, Version 22.0 (IBM Corp., Armonk, NY, USA). In the final analysis, four comparisons will be made: HIIT groups vs AC; HV-HIIT vs LV-HIIT; HV-HIIT vs AC; and LV-HITT vs AC. Two parametric tests will be performed after all assumptions for each test are met. For comparisons between groups at baseline, one-way analysis of variance (ANOVA) or the non-parametric method of Kruskal–Wallis and Chi-square test will be used. A linear regression model with ANOVA will be used to assess training effects on the primary and secondary study outcomes. We will examine the delta (Δ) score for each group (AC, HV-HIIT, LV-HIIT), adjusting for age, sex, changes in body mass, and the initial value of each of the dependent variables. Helmert contrasts will be performed to analyze the difference between the two exercise groups pooled together and the AC group. Bonferroni correction was used to determine the level of significance when a significant main effect was found. The differences between dropouts and participants who remain in the study will be examined; the data will be analyzed according to the intention-to-treat principle [50]. For each outcome variable, the effect size and the level of significance corresponding to the main group (between-subjects), time (within-subjects), and interaction (group × time) will be reported. To prevent type I error, post hoc comparisons (pre vs post by group) will be performed when a significant interaction effect is present. Values will be expressed as mean ± SD. The significance level will be set at 5% (α = 0.05). Practical significance will be assessed by calculating Cohen’s *d* effect size. Effect sizes (*d*) > 0.8, in the range of 0.5–0.8, in the range of 0.2–0.5, and < 0.2 will be considered as large, moderate, small, and trivial, respectively.

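### Withdrawal criterion (1) takes low attenders out of the trial before the primary test; its losses can fall only on the two HIIT arms, which contradicts the stated intention-to-treat analysis, and its threshold is ambiguous

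*Protocol article*

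**What the plan says.** Participant withdrawal introduces its list as "trial-related reasons for the participant to be discontinued from the trial by the principal investigator". Criterion (1) is "failure to maintain 80% compliance to exercise training sessions or even the last four weeks (minimum eight sessions), to avoid detraining". Criterion (2) is "more than two consecutive weeks without training, to avoid detraining".

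Under Exercise intervention program, the HIIT groups have two supervised sessions a week for 16 weeks, with telephone calls after missed sessions. Under Intervention/attention control, the AC group has no scheduled sessions: "participants will be advised to participate, without supervision". Its activity diary is encouraged, not required.

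Under Measurements: "The post-intervention test will be scheduled the following week after finishing the 16-week intervention period". Data analysis compares change scores between groups and states that "the data will be analyzed according to the intention-to-treat principle". It also says: "The differences between dropouts and participants who remain in the study will be examined". On losses: "Assuming a maximum loss of follow-up of 10%, the plan will be to recruit a total of 194 individuals".

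**The concern.** Two problems sit in one clause.

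The first is the consequence of a breach. It ends participation in the trial, not only the training or membership of a per-protocol set. A change score cannot be formed without the post-intervention test, and the article nowhere says that someone discontinued for low attendance is still tested. Attendance is measured after randomisation and exists in two of three arms, so the clause removes adherence-selected people from HIIT and nobody comparable from AC. If poor attenders gain less VO2peak, the remaining HIIT participants look better than the randomised group would have, in the direction of the trial's first hypothesis. Intention-to-treat exists to prevent this.

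The second is the threshold. The clause sets 80% and, for the last four weeks, a minimum that equals every scheduled session. The investigator of an open-label trial has to choose a reading, and the readings discontinue very different numbers of people.

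**Working it through.** **Inputs from the article.** Two sessions a week for 16 weeks; 80% compliance; last four weeks with a minimum of eight; planned mean changes 5.0, 5.0 and 3.0 with SD 4.0; alpha 0.05; 59 per arm; 194 to be recruited; 10% loss allowance.

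**Assumptions (the article gives no attendance figures).** Attendance per session 95% to 90%, no make-up sessions, no loss in AC. Sessions are independent unless stated.

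**The plan's own figure.** The between-group SD of means 5, 5, 3 is 0.943, so f = 0.943/4 = 0.236. The one-way ANOVA F test then needs N = 177, with power 0.801. The sample size reproduces and is not in dispute.

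**Session arithmetic.**
- Whole programme: 2 × 16 = 32 sessions; 0.8 × 32 = 25.6, so 26 are needed and six may be missed.
- Last four weeks: 2 × 4 = 8 sessions. A minimum of eight is 8/8 = 100%; 80% would be 6.4, so 7.

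**Share in breach under each reading.** The share of the whole trial is 2/3 of the per-arm share.

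| Reading | Formula | Per HIIT arm, 95% to 90% | Whole trial |
|---|---|---|---|
| (i) 8 of the last 8 | 1 − 0.95^8; 1 − 0.90^8 | 34% to 57% | 22% to 38% |
| (ii) 7 of the last 8 and 26 of 32 | P(<7 of 8 or <26 of 32) | 6% to 20% | 4% to 13% |
| (iii) 26 of 32 only | P(<26 of 32) | 0.1% to 4% | 0.1% to 2% |

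**Clustered absences.** With a beta-binomial model and within-person correlation 0.1 to 0.3, reading (iii) gives about 6-9% per HIIT arm at 95% attendance and 15-18% at 90%. Times 2/3, that is about 4-6% and 10-12% of the whole trial. At 90% attendance the mildest reading alone would use the 10% allowance.

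**Power (secondary).** 194/3 is about 65 per arm. Under (i), 65 × 0.663 = 43 remain per HIIT arm at 95% attendance and 65 × 0.430 = 28 at 90%. With 59 to 65 in AC, ANOVA power falls from 0.80 to 0.75-0.77 and to 0.65-0.68.

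**Can the bias be sized?** The rise in the HIIT mean from dropping breachers is the breach share times their shortfall in VO2peak gain against those who stay. The article gives neither factor. The two are also linked:
- With independent sessions under (i), breachers miss on average 8 × 0.05/0.337 = 1.2 late sessions at 95% attendance and 8 × 0.10/0.570 = 1.4 at 90%. Even if the whole planned gain of 5.0 were proportional to sessions attended, the shortfall would be only 1.2/32 × 5.0 = 0.19 to 1.4/32 × 5.0 = 0.22 mL/kg/min.
- A larger shortfall needs absences concentrated in particular people. Under that pattern fewer people breach (i): with (i) and the 80% rule together, 18-26% at 95% attendance and 34-47% at 90%.

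The direction can be argued; a figure cannot be read off the document.

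**The case against.** **The 8-of-8 reading is the least plausible.** A reader might infer that the plan demands perfect late attendance. Criterion (2) tolerates up to two consecutive weeks without training, and missed sessions are followed by telephone calls. Both fit a tolerant rule, and the bracket may simply describe a window that holds eight sessions. This stands: 100% is what the words literally say, but the document does not settle that it is meant. The high breach shares and the power loss belong to that reading only.

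**Scope.** A reader might infer that the whole withdrawal section acts only on HIIT, and only just before the test. That is too strong. Arm-specificity holds for criterion (1). Criterion (2) names no arm and could in principle be applied to AC, although unsupervised activity with an optional diary gives little to check it against. Timing just before the test fits the late clause; the 80% rule can be breached earlier, once a seventh session is missed.

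**A fuller document may cover it.** The article is condensed, it does commit to intention-to-treat, and criterion (4) names discontinuation and withdrawal from the study side by side, so the terms may differ. Further follow-up of discontinued participants may be described elsewhere. But the consequence stated here is discontinuation from the trial, and the analysis section separates dropouts from those who remain. An analysis plan can specify imputation; it cannot recover tests that the withdrawal rule itself prevents.

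**Adherence thresholds are usual in exercise trials.** They are, as per-protocol criteria. The fault lies in using one to end trial participation.

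**Conclusion.** The point holds for criterion (1). As written, it removes participants on attendance after randomisation, in the two HIIT arms only and before the primary outcome is measured, against the article's own intention-to-treat statement. That does not depend on how the threshold is read.

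The scale does. Under the assumed 95% to 90% attendance, the share in breach per HIIT arm runs from 0.1-4% to 34-57% across the readings with independent sessions. It is about 6-9% and 15-18% for the mildest reading if absences cluster. Without any loss in AC, the 10% allowance holds under the mildest reading with independent sessions. It is at risk at 90% attendance under the 7-of-8 reading or with clustering, and is exceeded throughout under 8 of 8. The direction of bias favours HIIT if non-adherers improve less. Its size is not derivable from the document, and none is claimed.

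**What to change.** Rewrite criterion (1):
- State one threshold: at least 26 of 32 sessions and, if a late criterion is wanted, at least 7 of the last 8. Say whether make-up sessions count.
- Treat a breach as low adherence, which defines a per-protocol set, and not as discontinuation from the trial.
- Invite every randomised participant to the post-intervention test and analyse as randomised.

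The cost is about one sentence, plus tests for people who would otherwise have been dropped. The target of 177 is unchanged, and a breach then uses none of the loss allowance.

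Recruitment was finishing when the article was submitted, so the change helps only those still in training, and tests already forgone cannot be recovered. For participants already discontinued under the rule, report which reading was applied and how many were discontinued, by arm.

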### Data analysis

The primary outcome variable of this study is VO_2peak_. A priori power analysis (G*Power 3 statistical software) [48] was performed to calculate the average sample size. Due to the lack of any source on the effect of VO_2peak_ in MI patients, we speculate a similar increase based on a study of coronary artery disease [49]. Therefore, we assume a mean change of 5.0 mL kg^−1^ min^−1^ and a common standard deviation (SD) of 4.0 for participants allocated to the HIIT groups and a mean change of 3.0 ± 4.0 mL kg^−1^ min^−1^ for participants allocated to the AC group. Based on 1:1:1 randomization to three treatment arms with equal group size, we expect that pre-post intervention differences in our design would be achieved with 177 people (59 each group, α = 0.05, Cohen medium effect size f = 0.23, 80% power). Assuming a maximum loss of follow-up of 10%, the plan will be to recruit a total of 194 individuals. The statistical analysis will be performed using IBM SPSS Statistics, Version 22.0 (IBM Corp., Armonk, NY, USA). In the final analysis, four comparisons will be made: HIIT groups vs AC; HV-HIIT vs LV-HIIT; HV-HIIT vs AC; and LV-HITT vs AC. Two parametric tests will be performed after all assumptions for each test are met. For comparisons between groups at baseline, one-way analysis of variance (ANOVA) or the non-parametric method of Kruskal–Wallis and Chi-square test will be used. A linear regression model with ANOVA will be used to assess training effects on the primary and secondary study outcomes. We will examine the delta (Δ) score for each group (AC, HV-HIIT, LV-HIIT), adjusting for age, sex, changes in body mass, and the initial value of each of the dependent variables. Helmert contrasts will be performed to analyze the difference between the two exercise groups pooled together and the AC group. Bonferroni correction was used to determine the level of significance when a significant main effect was found. The differences between dropouts and participants who remain in the study will be examined; the data will be analyzed according to the intention-to-treat principle [50]. For each outcome variable, the effect size and the level of significance corresponding to the main group (between-subjects), time (within-subjects), and interaction (group × time) will be reported. To prevent type I error, post hoc comparisons (pre vs post by group) will be performed when a significant interaction effect is present. Values will be expressed as mean ± SD. The significance level will be set at 5% (α = 0.05). Practical significance will be assessed by calculating Cohen’s *d* effect size. Effect sizes (*d*) > 0.8, in the range of 0.5–0.8, in the range of 0.2–0.5, and < 0.2 will be considered as large, moderate, small, and trivial, respectively.

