**Methods/Design:**

In this randomized controlled trial, cardiorespiratory fitness, anthropometry, central and peripheral cardiovascular variables, biochemical and nutritional condition, and quality of life will be assessed before and after 16 weeks of intervention in 177 participants diagnosed with MI type 1. All participants will be randomly (1:1:1) assigned to the attention control group or two exercise groups (Mediet recommendations plus supervised aerobic exercise two days/week: (1) HV (40 min) HIIT group and (2) LV (20 min) HIIT group.

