### Participants and selection criteria

The population will include 177 participants (men and women) with the diagnosis of MI according to criteria of “Third Universal definition of myocardial infarction” and clinical classification of MI type 1, called “Spontaneous myocardial infarction” [1], recruited from the cardiology services by the physician specialists. In turn, before testing protocol begins, an ergometry is performed according to the clinical history for participants’ screening to ensure there is no ongoing myocardial ischemia. After completion of the informed consent process, clinical history, blood sample for baseline analysis, electrocardiogram, and echocardiogram are obtained from all participants to evaluate the eligibility criteria. Only participants who have been managed with revascularization are included. The inclusion and exclusion criteria for the INTERFARCT study are shown in Table 1. After assessment for eligibility and consent, different clinical research members collect the baseline data necessary to complete the pre-randomization information.

**Table 1 Tab1:** Inclusion and exclusion criteria for the INTERFARCT study

Inclusion criteria
- MI type I: Spontaneous MI [1], with and without ST elevation
- Effective revascularization treatment (coronary artery bypass grafting or percutaneous coronary intervention)
- Age ≥ 18 years, clinically stable on sinus rhythm
- Between six months and two years after the MI
- Left ventricular ejection fraction > 50%
- Time availability (45 min, two days a week for 16 weeks) to carry out the exercise program
Exclusion criteria
- Unstable coronary artery disease, uncontrolled hypertension, malignant ventricular arrhythmia, atrial fibrillation, exercise-induced ischemia, and ventricular failure during exercise

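### The article uses 177 both as the number the power calculation needs and as the number recruited or randomised, against a recruitment plan of 194, and 194 is itself slightly too few for 10% loss

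*Protocol article*

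**What the plan says.** The Data analysis section assumes mean changes in VO2peak of 5.0 mL/kg/min in the HIIT groups and 3.0 in the attention control group, with an SD of 4.0 throughout and three equal arms. It arrives at 177 people, with these settings: "59 each group, α = 0.05, Cohen medium effect size f = 0.23, 80% power". It then allows for attrition: "Assuming a maximum loss of follow-up of 10%, the plan will be to recruit a total of 194 individuals".

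Two other places give a sample size. The section on participants and selection criteria says: "The population will include 177 participants (men and women) with the diagnosis of MI", and adds that they are recruited from the cardiology services. The Methods/Design paragraph of the Abstract says that outcomes "will be assessed before and after 16 weeks of intervention in 177 participants diagnosed with MI type 1". Its next sentence has all participants randomised 1:1:1. Neither place mentions 194 or says that 177 means people with complete data.

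The Trial status section reports that recruitment is nearly complete.

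**The concern.** In the Data analysis section, 177 is what must remain after losses and 194 is what must be recruited. In the other two places, 177 is what goes in. A reader cannot tell which number defines full enrolment, and so cannot judge later whether the trial reached its target. If 177 is the number randomised, nothing is left to absorb the 10% loss that the protocol itself allows for, and the evaluable sample falls below the number on which 80% power rests.

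The step from 177 to 194 also looks wrong in its own right. To keep 177 after losing 10%, one divides by 0.9. Multiplying by 1.1 gives too small a number.

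**Working it through.** **Inputs, all from the Data analysis section:** mean changes of 5.0, 5.0 and 3.0; common SD 4.0; three equal arms; α = 0.05; target power 80%; loss 10%.

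**Step 1: reproduce 177.**
- Grand mean = (5 + 5 + 3)/3 = 4.333.
- SD of the group means = √[(0.667² + 0.667² + 1.333²)/3] = √0.8889 = 0.9428.
- f = 0.9428/4.0 = 0.2357.
- Power of the one-way ANOVA F test comes from the noncentral F distribution with 2 and N − 3 degrees of freedom and noncentrality λ = f²N.
- At N = 177, λ = 0.05556 × 177 = 9.83 and power = 80.1%. Stepping N by 3, 177 is the first value to reach 80%.

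The plan's 177 is therefore reproduced exactly, and it is the number analysed, with no allowance for loss.

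**Step 2: the inflation for loss.**
- Required: 177/(1 − 0.10) = 196.7, so 197. For three equal arms this becomes 198 (66 per arm).
- Multiplying instead: 177 × 1.10 = 194.7, which cut to a whole number is the stated 194.
- Check: 194 × 0.90 = 174.6, so about 174 remain, while 197 × 0.90 = 177.3. Also, 194 does not divide by three.

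**Step 3: power under each reading of the enrolment number** (f = 0.2357, α = 0.05, 10% lost).

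| Randomised | Remaining after 10% loss | Power, three-group test |
|---|---|---|
| 197 | 177 | 80.1% |
| 194 | 174 | 79.4% |
| 177 | 159 (177 × 0.9 = 159.3) | 75.4% |

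**Step 4: the printed effect size.** The text prints "Cohen medium effect size f = 0.23". The value from the stated means and SD is 0.2357, which rounds to 0.24, so 0.23 is a truncation. Entered as if exact, 0.23 gives 78.0% power at 177 and requires 186 for 80%. Those figures describe the shortened display value, not the assumptions stated beside it.

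**The case against.** The strongest defence is that the Data analysis section is the only place that sets a recruitment target, and it separates the number needed from the number to recruit. On that plan the slip costs at most 0.6 of a percentage point (79.4% against 80%). The 10% is described as a maximum, and 177 would still remain with up to 17 of 194 lost (8.8%). The first Abstract sentence, on assessment before and after the intervention, can also be read as describing people with both measurements.

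Much of this stands. The 194 plan delivers its stated power for practical purposes. It does not remove the inconsistency, because the Abstract goes on to randomise all its participants and the participants section describes 177 as recruited.

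It is also fair to say that 75.4% refers to the unadjusted three-group test. The planned contrast of the pooled HIIT groups with control is better placed: on the same assumptions, with a two-sided 5% level and no Bonferroni correction, its power is about 84% at 159 and 87% at 174. The adjustment for baseline value, age and sex is not counted either. However, the protocol's own calculation, with f and 59 per group, is for the three-group test, so that is the right yardstick for its 80% claim.

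A reader might go further and infer that the printed f fails to support 177, or that 80% power is not delivered as the plan is written. The document supports neither. The means and SD in the same section give 177 exactly, and under the stated plan to recruit 194 the shortfall is negligible.

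**Conclusion.** The point holds as an inconsistency in a basic design figure, together with a small arithmetic slip. The number to be randomised is 194 in the Data analysis section and 177 elsewhere, and 10% loss in fact calls for 197 (198 with equal arms).

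A material loss of power, from 80% to about 75%, arises only if 177 is the number actually randomised and the full 10% is lost. The article does not show that this happened or will happen. The power figures rest on the protocol's own means and SD, on the unadjusted three-group test at 5%, and on lost participants contributing no VO2peak change to the analysis. The derivation of 177 is not in question.

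**What to change.** - In the Data analysis section, label 177 as the evaluable number, and replace 194 with 197, or 198 (66 per arm) for equal groups.
- Give that same randomised number in the Abstract and in the section on participants and selection criteria.
- If enrolment closes at 177 or 194, do not extend it. Report the number actually randomised in all three places and restate the power of the three-group test under 10% loss as about 75% or 79% respectively.
- In the same edit, the effect size may be printed as 0.236, so that a reader who enters it recovers 177.

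The cost is a text correction and, if enrolment closes at 177 or 194, a slightly less favourable stated power. Nothing in the design or analysis changes.
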